### 2.9. Statistical Analysis

Normally distributed quantitative variables will be presented with mean, standard deviation, and 95% confidence interval. Non-normally distributed data will be presented with median and interquartile ranges. The difference between intracoronary indices values before and after TAVI will be assessed with Student *t* or Mann–Whitney *U* tests as appropriate. Sensitivity, specificity, positive predictive value (PPV), and negative predictive value (NPV) of intracoronary indices measured in LAD will be calculated on a per-patient basis. Receiver operator characteristic (ROC) curves will be constructed for FFR, CFR, and IMR to determine diagnostic cut-off values. Correlations between intracoronary indices and MBF measured by CZT-SPECT will be assessed using Pearson’s correlations. A statistically significant difference will be defined as a two-sided *P* value less than 0.05. The missing data will be labelled.

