## 2. Materials and Methods

### 2.1. Study Design

We are planning to enroll 40 patients, all of whom have a clinical indication to elective TAVI, as jointly evaluated by the local Heart Team, and are diagnosed with intermediate stenosis (30–70%) in the left anterior descending (LAD) artery. We will measure FFR, CFR, and IMR before, and either immediately after (Group I) or 6 months after (Group II) TAVI. At the same time, myocardial perfusion will be assessed by CZT- SPECT, to compare intravascular indices to myocardial perfusion results (Figure 1).

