### 2.2. Study Objectives

The primary objective is to measure FFR, CFR, IMF, and myocardial perfusion CZT-SPECT before the TAVI procedure and either immediately after TAVI or after 6 months, to specify the acute and long-term changes in coronary pressure and flow. The secondary objective is to compare FFR, CFR, and IMR to myocardial perfusion CZT-SPECT to identify cut-off values of CFR, IMR, and FFR defining significant stenosis (Figure 2).

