### 2.4. Sample Size

Our target sample size is set at 40 patients for a proof-of-concept study. No power calculations were performed since this is currently a pilot study and relevant data on our research objectives regarding the comparison between patients suffering from AS with CFR and IMR assessment are lacking. The results of this study will be used to design a larger study in the near future. Since the total number of patients for AS diagnosis in the Division of Cardiology and Structural Heart Diseases is estimated at 100 a year, we expect that our target number of patients can be included within one year.

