### 2.5. Patient Recruitment

When all inclusion criteria are met, the patient will be asked by the physician to participate in the study. After signing the informed consent, each patient will undergo rest and stress CZT-SPECT and coronary angiography with measurement of FFR, CFR, and IMR. This diagnostic process will be repeated immediately after TAVI (Group I) or 6 months later (Group II).

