## 4. Limitations

This study has several limitations. First, this is a proof-of-concept study with a small sample size. Nevertheless, the number of patients enrolled enables us to derive cut-off values for intracoronary indices and to design a study with an increased sample size in the future. Second, patients will be randomized into two groups—in the first one an acute change in intracoronary indices will be analysed, and in the second one, a long-term change. The decision to randomise patients into two groups instead of analysing acute and long-term changes in each participant was to decrease the radiation exposure. Third, one may argue that magnetic resonance or positron emission tomography (PET) should be used to validate intracoronary indices. Importantly, we plan to use CZT-SPECT which enables quantitative analysis of coronary flow reserve and it was found to be a feasible tool in myocardial blood flow analysis as compared to showing a good correlation with [19] ammonia-PET [34,35].

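### The before/after TAVI comparison is paired, but section 2.9 names Mann–Whitney U, an independent-samples test, and does not say that its Student t is paired

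*Protocol article*

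**What the plan says.** Section 2.1 sets out two measurements per patient: "We will measure FFR, CFR, and IMR before, and either immediately after (Group I) or 6 months after (Group II) TAVI". Section 2.5 confirms that the work-up is done again in the same person: "This diagnostic process will be repeated immediately after TAVI (Group I) or 6 months later (Group II"). Section 2.3 limits the assessment to the LAD. Section 4 states that "patients will be randomized into two groups", one for the acute change and one for the long-term change.

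The aim of the repeat measurement is given in section 2.2: "to specify the acute and long-term changes in coronary pressure and flow". The before/after comparison is therefore the analysis that serves the primary objective.

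Section 2.9 assigns the test. "The difference between intracoronary indices values before and after TAVI" "will be assessed with Student *t* or Mann–Whitney *U* tests as appropriate", with significance at a two-sided 0.05. The article names no paired t-test, signed-rank test or repeated-measures model anywhere.

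**The concern.** Every post-TAVI value has a pre-TAVI partner from the same patient and the same vessel. A two-sample test discards that link and judges the mean change against the full spread between patients instead of the spread of the within-patient changes. When the two measurements are positively correlated, as one expects on re-measuring one vessel, the standard error comes out too large and real changes are more easily missed.

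This matters because of how a null result would be read. The Introduction describes conflicting evidence on whether FFR changes after TAVI, and reports that non-significant changes have been taken as support for using FFR in aortic stenosis. The Discussion adds that small shifts matter most for borderline lesions. A test with avoidably low power could supply another non-significant result open to the same reading. Section 2.4 also says that the results will be used to design a larger study, which needs the variability of the within-patient change.

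**Working it through.** **Step 1: match the test to the data.**

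| Feature | Protocol article | Consequence |
|---|---|---|
| Unit measured | Same patient, before and after (2.1, 2.5) | Paired |
| Vessel | LAD only (2.3) | One pair per patient and index |
| Contrast tested | Before vs after TAVI (2.9) | Within-patient change |
| Rank test named | Mann–Whitney U (2.9) | For independent samples; the matched counterpart is the Wilcoxon signed-rank test |
| t-test named | Student t, unqualified (2.9) | Pairing not stated |

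The closing words of the test sentence follow two sentences that separate normal from non-normal data. They read as a choice by distribution, not a choice between paired and unpaired tests.

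**Step 2: inputs for the size of the loss.**
- From the article: 40 patients in total (2.4), two groups (4), two-sided 0.05 (2.9).
- Assumed, because the article gives no figure: a 1:1 split, so 40/2 = 20 pairs per group; equal SDs; bivariate normal data; a true change of 0.5 SD; within-patient correlation ρ from 0.3 to 0.9.
- The article states no power, effect size or SD, so there is no figure of its own to reproduce.

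**Step 3: standard error and interval width.** With SD σ at each time and n pairs:
- unpaired SE = σ√(2/n)
- paired SE = σ√(2(1−ρ)/n)
- SE ratio = 1/√(1−ρ)

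The confidence-interval ratio also needs the critical values: t with 38 df = 2.02 unpaired and t with 19 df = 2.09 paired, a factor of about 0.967. For example, at ρ = 0.7 the ratio is 1.83 × 0.967 = 1.77.

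| ρ | SE ratio | CI-width ratio |
|---|---|---|
| 0.3 | 1.20 | 1.16 |
| 0.5 | 1.41 | 1.37 |
| 0.7 | 1.83 | 1.77 |
| 0.8 | 2.24 | 2.16 |
| 0.9 | 3.16 | 3.06 |

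**Step 4: power for a 0.5 SD change, by simulation.** Figures carry about one percentage point of simulation error.

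| ρ | Unpaired t | Paired t | Mann–Whitney U | Signed-rank |
|---|---|---|---|---|
| 0.3 | 32% | 44% | 30% | 42% |
| 0.5 | 29% | 56% | 28% | 55% |
| 0.7 | 24% | 78% | 24% | 76% |
| 0.8 | 22% | 92% | 22% | 90% |
| 0.9 | 17% | >99% | 20% | >99% |

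The noncentral t distribution gives paired powers of 43.4%, 56.5%, 78.2%, 91.8% and 99.7%, in agreement. At ρ = 0 paired and unpaired tests perform about equally (32% vs 33% for t), as they should.

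**Step 5: type I error.** With no true change, the unpaired t rejects in about 2% of trials at ρ = 0.3, 0.8% at 0.5 and 0.1% at 0.7, against a nominal 5%. The paired t stays at 5%.

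**Step 6: sensitivity.** For a smaller change of 0.3 SD, unpaired vs paired t power is 8% vs 25% (ρ = 0.5), 4% vs 38% (0.7) and 2% vs 52% (0.8). Pooling all 40 pairs does not remove the loss: at 0.3 SD and ρ = 0.7 it is 14% vs 67%.

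**The case against.** **A paired t-test is also a Student t-test.** This is fair and it stands. A reader might infer that both named tests are unpaired as a matter of fact. The text does not establish that for the t-test, and a condensed article can leave its pairing to the full plan. What the article does establish is that the rank test is wrong. That is a stated method, not a missing detail, and nothing elsewhere in the article corrects it.

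**Mann–Whitney U may be meant for comparing changes between Groups I and II.** It would suit that contrast, but the sentence applies it to values before and after TAVI.

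**The loss depends on assumptions.** This also stands. The article gives no correlation, effect size, SD or allocation ratio. A high correlation cannot be presumed for CFR or IMR, or over a 6-month interval. At ρ = 0.3 the loss is modest, which is why the range starts there.

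**The error is on the safe side.** It is true that false positives do not rise, and that the estimated mean change is the same under either t-test. A reader might infer that the estimate is biased or that false positives are inflated; neither follows. The harm is lost power and intervals that are too wide.

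**This is a pilot with no power calculation.** "Our target sample size is set at 40 patients for a proof-of-concept study" explains the small size. It does not justify a test that discards the pairing, since section 2.9 still sets a significance threshold for this comparison.

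**Perfusion is not covered by the test sentence.** A reader might infer from section 2.2, where "The primary objective is to measure FFR, CFR, IMF, and myocardial perfusion CZT-SPECT before the TAVI procedure", that the change in SPECT perfusion has no analysis. The Introduction defines the first endpoint by FFR, IMR and CFR alone, and a condensed article may leave a perfusion test to the full plan. It is not part of this point.

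**Conclusion.** Wrong as written for the non-normal branch, and unclear for the normal branch. If the comparison is run unpaired, it is conservative and loses power on the primary objective for any meaningful positive within-patient correlation. Under the assumed 20 pairs per group and 0.5 SD change, the loss for the t-test runs from about 12 percentage points (44 − 32) at ρ = 0.3 to more than 80 (over 99 against 17) at ρ = 0.9. The rank tests lose nearly as much, and the t-based interval is about 1.16 to 3.06 times too wide over the same range. The direction does not rest on the assumed effect size or split; the size does. It does not follow that the study will miss a real change, only that its chance of doing so is needlessly raised.

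**What to change.** Replace the before/after sentence in section 2.9 with:

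> Within each group, the change from before to after TAVI will be tested with a paired t-test on within-patient differences or, if the differences are clearly non-normal, the Wilcoxon signed-rank test, and the change will be reported with its 95% CI.

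Judge normality on the within-patient differences, not on the raw values at each time. If a full analysis plan already specifies a paired t-test, only the rank test needs correcting there, and the two texts should be aligned.

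Cost: one sentence, settled before analysis. It needs no extra patients, procedures or data.

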## 3. Discussion

In our study, we will investigate the immediate and long-term changes of FFR, CFR, and IMR after TAVI, and compare these results with measurements acquired before the TAVI procedure. As a next step, we aim to validate FFR, CFR, and IMR against myocardial perfusion SPECT. Therefore, this study will help to determine the influence of severe AS on intermediate coronary artery lesion severity which is still not fully understood. As a result, intravascular indices might be used to guide decision-making on revascularisation in patients with severe AS and concomitant CAD.

The narrowed area of the aortic valvular orifice reduces the blood flow from the left ventricle and causes a pressure drop in the aorta. As a result, the pressure load in the left ventricle and within the left ventricular wall is increased and driving forces of coronary flow are decreased. The increased intraventricular pressure creates a force that reduces the blood flow from the subepicardium to the subendocardium [20]. Both reduced coronary flow during systole and decreased subendocardial perfusion cause preferential epicardial blood flow and ‘blood flow mismatch’ which results in myocardial ischaemia [21,22]. Moreover, due to the fact that FFR, CFR, and IMR are measured during the entire cardiac cycle, each of them is influenced by prolonged systole in severe AS. Therefore, the physiological assessment of coronary artery stenosis in this group of patients remains challenging.

In clinical practice, FFR is used as a gold standard to determine significant coronary artery stenosis in intermediate lesions [23,24]. In patients with severe AS, the accuracy of FFR has not been confirmed, therefore guidelines still support ICA as a gatekeeper for revascularisation in this group of patients [12]. Importantly, in patients with AS the correlation between angiographic and hemodynamic significance of coronary artery stenosis is mild and the specificity and positive predictive value of ICA in the detection of significant stenosis is low, especially in LAD [25,26].

It was previously found that FFR is underestimating coronary stenosis severity in patients before TAVI because it decreases within the same coronary lesion after the TAVI procedure [6]. Some studies reported that the change in FFR after TAVI is minor. However, as underlined by Vendrik and colleagues, these minor discrepancies are the main challenge in borderline FFR results. At the same time, these borderline lesions are also the most challenging in ICA assessment. Therefore, the main problem remains unsolved. Currently, several ongoing trials will compare FFR-guided revascularization to angiography-guided revascularization in patients with severe-AS (FAITAVI (Functional Assessment in TAVI); (NOTION-3)) which hopefully will shed light on further management of patients with severe AS and concomitant CAD. Unfortunately, none of these trial implements offer invasive indices or non-invasive imaging methods which may improve the assessment of coronary artery stenosis.

In patients with severe AS, an increased resting flow enables adequate perfusion at rest, but not during stress. That was reflected in previous studies which showed that resting blood flow velocity in patients with AS is almost 18% higher and hyperaemic flow is 34% lower as compared to the control group [27,28]. Consequently, the increased baseline flow and reduced hyperaemic flow result in CFR reduction. As far as IMR is concerned, the decrease in myocardial resistance at rest has been demonstrated in patients with AS [29]. However, there was no difference between the control group and patients with AS in hyperaemic IMR values [30]. As explained by Lumley and colleagues, ischemia in patients with severe AS was not caused by microvascular dysfunction, but by abnormal coronary coupling which affects both FFR and CFR, but not IMR [30]. All things considered, the effect of AS on coronary flow and microvasculature still needs to be clarified.

In previous studies, FFR was validated against myocardial perfusion SPECT, revealing a cut-off value higher than in patients without severe AS [31]. Importantly, so far a semiquantitative SPECT was used which does not allow for myocardial blood flow quantification. In our study, CZT -SPECT will be applied which provides a quantitative analysis of myocardial blood flow and myocardial flow reserve (MFR) which provides a more accurate assessment of multivessel and microvascular disease [32,33].

Notwithstanding the clinical value of previous studies, patients with both stenotic and non-stenotic coronary arteries were included, indices were measured in different coronary arteries and directly after the implantation of the aortic valve, and there was no comparison of all three indices with non-invasive imaging. It goes without saying that FFR, CFR, and IMR together provide a broad overview of myocardial hemodynamics which may help to understand the influence of AS on the assessment of CAD. Therefore, we aim to analyse FFR, IMR, and CFR in the left anterior descending coronary artery, immediately after TAVI and in 6 months, and compare these results to CZT-SPECT analysis. If the combination of CFR, IMF, and FFR will be accurate for the coronary assessment in patients suffering from AS, we may imply these methods in daily practice to determine patients who may benefit from revascularisation.

## 4. Limitations

This study has several limitations. First, this is a proof-of-concept study with a small sample size. Nevertheless, the number of patients enrolled enables us to derive cut-off values for intracoronary indices and to design a study with an increased sample size in the future. Second, patients will be randomized into two groups—in the first one an acute change in intracoronary indices will be analysed, and in the second one, a long-term change. The decision to randomise patients into two groups instead of analysing acute and long-term changes in each participant was to decrease the radiation exposure. Third, one may argue that magnetic resonance or positron emission tomography (PET) should be used to validate intracoronary indices. Importantly, we plan to use CZT-SPECT which enables quantitative analysis of coronary flow reserve and it was found to be a feasible tool in myocardial blood flow analysis as compared to showing a good correlation with [19] ammonia-PET [34,35].

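### The claim that 40 patients are enough to derive cut-offs has no precision basis; cut-offs and accuracy read from one small cohort will be imprecise and optimistic

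*Protocol article*

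**What the plan says.** **Sample size.** Section 2.4 of the protocol article states: "Our target sample size is set at 40 patients for a proof-of-concept study". It adds: "No power calculations were performed since this is currently a pilot study". The declared use is stated in the same section: "The results of this study will be used to design a larger study in the near future".

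**Sufficiency.** Section 4 (Limitations) first concedes the point: "First, this is a proof-of-concept study with a small sample size". The next sentence turns the concession round by saying that "the number of patients enrolled enables us to derive cut-off values for intracoronary indices", and that a bigger study can then be designed.

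**Analysis.** Section 2.9 says: "Receiver operator characteristic (ROC) curves will be constructed for FFR, CFR, and IMR to determine diagnostic cut-off values". Just before that, it says that sensitivity, specificity, PPV and NPV "of intracoronary indices measured in LAD will be calculated on a per-patient basis".

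**Status and use of the cut-offs.** They are the secondary endpoint (Introduction) and the secondary objective (section 2.2). The Abstract and the Conclusions present them as something the study will deliver. The Discussion adds that, if the three indices together prove accurate, "we may imply these methods in daily practice to determine patients who may benefit from revascularisation".

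**The concern.** The Limitations sentence is a positive statement about what the sample can do, and nothing in the article supports it. No AUC, no proportion of patients with reduced flow on CZT-SPECT and no target interval width is given.

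Two separate problems follow if section 2.9 is carried out as it reads:

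- A threshold picked because it performs best in a sample looks better in that sample than it will in new patients.
- The threshold itself moves a great deal from one sample of 40 to the next.

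The accuracy figures would therefore look too good, and the cut-offs would be printed with more authority than they have. The practical risk lies in the next study. If it is planned on uncorrected sensitivity and specificity, it could be too small. A reader could also take the published thresholds as usable.

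**Working it through.** **What can be reproduced.** Nothing. The figure of 40 comes with no effect size, AUC, prevalence or precision target. The check therefore asks what 40 patients can deliver.

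**Inputs from the document.** N = 40 (section 2.4); one cohort; cut-offs from ROC curves (section 2.9).

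**Assumptions not in the document.** One observation per patient; 8 to 20 reference-positive patients; true AUC 0.70 to 0.80; equal-variance normal index, oriented so that higher means abnormal; cut-off at maximum J = sensitivity + specificity − 1 (Youden); and, for one illustration only, an FFR within-group SD of 0.08.

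**Step 1: true accuracy under the model.** Separation d = √2 × Φ⁻¹(AUC). At cut-off c, sensitivity = Φ(d − c) and specificity = Φ(c). The best cut-off is d/2, with J = 2Φ(d/2) − 1.

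- AUC 0.80: d = 1.414 × 0.842 = 1.19; best cut-off 0.60; best J = 0.45.
- AUC 0.70: d = 1.414 × 0.524 = 0.74; best cut-off 0.37; best J = 0.29.

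**Step 2: select and evaluate in the same 40.** Monte Carlo, 3,000 replicates per row. Apparent J is computed in the sample; true J is the model value at the selected cut-off. Differences are taken before rounding.

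| AUC | Positives of 40 | Apparent J | True J | Overstatement | 95% range of cut-off (SD) | Width (SD) |
|---|---|---|---|---|---|---|
| 0.70 | 8 | 0.45 | 0.25 | 0.19 | −0.71 to 1.53 | 2.24 |
| 0.70 | 12 | 0.42 | 0.26 | 0.16 | −0.68 to 1.46 | 2.14 |
| 0.70 | 20 | 0.41 | 0.26 | 0.15 | −0.62 to 1.38 | 2.00 |
| 0.80 | 8 | 0.59 | 0.41 | 0.18 | −0.25 to 1.60 | 1.85 |
| 0.80 | 12 | 0.57 | 0.41 | 0.15 | −0.25 to 1.51 | 1.76 |
| 0.80 | 20 | 0.55 | 0.42 | 0.14 | −0.25 to 1.44 | 1.69 |

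With AUC 0.75 and 12 positives, apparent J is 0.49 against a true 0.33. Over the full grid (AUC 0.70, 0.75 and 0.80; 8, 12, 16 and 20 positives) and repeat runs, the overstatement is about 0.13 to 0.20 and the width about 1.7 to 2.3 SD.

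**Step 3: what that width means.** At AUC 0.80 with 12 positives:

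- c = −0.25: sensitivity Φ(1.44) = 0.93, specificity Φ(−0.25) = 0.40.
- c = 1.51: sensitivity Φ(−0.32) = 0.37, specificity Φ(1.51) = 0.93.

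On the FFR scale, 1.7 × 0.08 = 0.14 and 2.3 × 0.08 = 0.18 FFR units.

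**Step 4: how good the selected cut-off is on average.** At AUC 0.80 with 12 positives, mean true J is 0.41 against the optimum of 0.45. At AUC 0.70 it is 0.26 against 0.29. The average loss is about 0.03 to 0.04.

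**Step 5: precision even with no selection.** Clopper–Pearson limits for x of n are the 2.5% point of Beta(x, n − x + 1) and the 97.5% point of Beta(x + 1, n − x). An observed sensitivity of 75% gives 43 to 95% for 9 of 12, and 51 to 91% for 15 of 20.

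For the AUC (Hanley–McNeil), with A = 0.80, 12 positives and 28 negatives: Q1 = A/(2 − A) = 0.667 and Q2 = 2A²/(1 + A) = 0.711. The variance is [0.16 + 11 × (0.667 − 0.64) + 27 × (0.711 − 0.64)]/336 = 0.0071, so SE = 0.084 and the half-width is 1.96 × 0.084 = 0.16. Over the grid the half-width is about 0.14 to 0.22.

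**Step 6: scale.** At AUC 0.80 and 30% positives, the overstatement falls from 0.15 at N = 40 to 0.10 at 80, 0.06 at 200 and 0.04 at 400.

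**The case against.** The strongest reply is that this is an openly small pilot. Read whole, the Limitations passage concedes the sample size and points to a bigger study. Having made no power calculation does not contradict being able to obtain exploratory values. Section 2.9 names no rule for choosing the threshold, and its accuracy sentence comes before the ROC sentence without being tied to the derived cut-offs. Interval methods and optimism correction are usual content of an analysis plan, and that plan is not shown.

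Much of this stands. Same-sample evaluation and the Youden rule are inferences, and the article's silence on correction methods is not itself the fault. What remains is that the article asserts sufficiency without a basis, and that the procedure as it reads, in the only cohort there is, leads to optimistic figures.

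Three stronger readings are tempting, and the documents do not support them:

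- A reader might infer that the cut-offs will be close to arbitrary. Step 4 shows otherwise: for an index that discriminates, the selected cut-off loses little on average. Only an index with no discrimination gives a truly arbitrary one; it would still show an apparent J of about 0.17 to 0.22.
- A reader might infer that excluding coronary disease that needs revascularisation (Table 1) leaves few reference-positive patients. No prevalence is given. The reference is SPECT flow reserve, and the Discussion says aortic stenosis itself lowers flow reserve, so positives could be common.
- A reader might infer that the authors intend to put these cut-offs straight into practice. The daily-practice sentence is conditional on accuracy and concerns the combination of indices. It matters here only because that condition might be judged on optimistic figures.

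**Conclusion.** The point holds in a limited form. The claim that 40 patients suffice to derive cut-offs is unsupported, and choosing and judging cut-offs in that one cohort would overstate sensitivity plus specificity by about 0.13 to 0.20, with cut-offs uncertain over about 1.7 to 2.3 within-group SDs.

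The size depends on the assumed AUC, number of positives, binormal form and Youden rule. The upward direction does not, for any threshold chosen to maximise accuracy in the data used to assess it. The calculation takes the favourable case in which all 40 patients contribute to each curve.

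This should be corrected but is not critical: it affects a secondary endpoint of a declared pilot and leaves the before-and-after comparison untouched. An analysis plan that is not shown may already contain the correction; the Limitations wording would still need changing.

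**What to change.** 1. **Limitations (section 4).** Replace the sufficiency statement with one saying that the sample yields exploratory cut-offs only, that their confidence intervals are expected to be wide, and that they need external validation.
2. **Statistical Analysis (section 2.9).** For each index, report the AUC with a 95% CI, a bootstrap CI for the cut-off, and optimism-corrected sensitivity and specificity. The threshold must be selected again inside every bootstrap sample; otherwise the correction misses the selection step. If the analysis plan already does this, a cross-reference is enough.
3. **Larger study (section 2.4).** State that only the corrected estimates, with their intervals, will be used in its design.

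The cost is a few sentences and a small amount of extra programming, with no additional patients or measurements. The real price is that the reported accuracy will look less favourable.

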## 1. Introduction

Aortic stenosis (AS) is the most common valvular disease, and the number of patients is set to double in the next 20 years [1]. Importantly, in 30–68% of patients diagnosed with AS, coronary artery stenosis is also present [2].

In clinical practice, the severity of coronary artery stenosis and microvasculature dysfunction can be assessed by means of fractional flow reserve (FFR), coronary flow reserve (CFR), and index of microvascular resistance (IMR). However, in patients with AS, the assessment of coronary flow is impaired due to volume and pressure overload of the left ventricle. Moreover, in patients with AS and concomitant coronary artery disease (CAD) not a single stenosis but tandem stenosis is present—first is the aortic stenosis, and second is the coronary artery stenosis. As a result, the hyperaemic flow in coronary arteries is changed which affects the measurement of coronary artery hemodynamics [3].

Transcatheter aortic valve implantation (TAVI) allows the rapid unloading of the left ventricle and can acutely affect coronary flow. As reported by Pesarini et al. and Lunardi et al., changes in FFR after transcatheter aortic valve implantation (TAVI) were insignificant, indicating that this tool can be used to guide revascularisation in AS patients [4,5]. On the other hand, the underestimation of coronary stenosis by hyperemic indices was found in most of the studies conducted so far [6,7,8,9,10]. The discrepancy between findings and lack of evidence is reflected in current guidelines, which still maintain coronary angiography as a standard to guide revascularization [11,12].

All things considered, the physiological assessment of intermediate coronary artery stenosis severity in patients with severe AS is still a real challenge. Therefore, the aim of this study is to investigate the changes in FFR, CFR, IMR, and myocardial perfusion in patients with severe AS after TAVI. As a first endpoint, we will assess acute and long-term changes in FFR, IMR, and CFR in patients undergoing the TAVI procedure. The secondary endpoint is to determine cut-off values of intracoronary indices defining significant stenosis based on myocardial perfusion measured by cadmium-zinc-telluride single-photon emission tomography (CZT-SPECT), in patients with severe AS and concomitant CAD.

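### Patients are randomised to acute or 6-month reassessment, but the stated before/after test uses neither the randomised comparison nor the baselines of both groups

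*Protocol article*

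**What the plan says.** Section 2.1 gives every patient a baseline and one follow-up: "We will measure FFR, CFR, and IMR before, and either immediately after (Group I) or 6 months after (Group II) TAVI". Section 4 adds that allocation between the two is random: "patients will be randomized into two groups—in the first one an acute change in intracoronary indices will be analysed", with the second group serving the long-term change. The reason given for splitting the patients, "instead of analysing acute and long-term changes in each participant was to decrease the radiation exposure", is safety rather than a comparison between groups.

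The first endpoint, in the Introduction, is that "we will assess acute and long-term changes in FFR, IMR, and CFR in patients undergoing the TAVI procedure". Section 2.9 meets it with one sentence: "The difference between intracoronary indices values before and after TAVI will be assessed" by Student t or Mann–Whitney U, at a two-sided 0.05 level. The sentence does not say whether the test is paired or run by group. On incomplete data the section says only: "The missing data will be labelled". Section 2.4 states: "Our target sample size is set at 40 patients for a proof-of-concept study", and "No power calculations were performed since this is currently a pilot study".

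**The concern.** Randomising the time of reassessment makes the two groups comparable at baseline, apart from chance. That allows two things which a before/after test does not use. The acute and late effects can be contrasted directly, and all 40 baselines can inform the estimate of change in each group.

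The contrast is a natural question for this study. The Discussion notes that earlier work measured indices directly after valve implantation, and presents measurement at both times as part of what this study adds. Readers will want to know whether the late change differs from the acute one. With only before/after tests, the material for an answer would be two separate results, and one significant result beside one non-significant result is not evidence of a difference.

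**Working it through.** **Inputs.** From the documents: 40 patients, two randomised groups, one baseline and one follow-up each, two-sided 0.05. Assumed, because the documents do not give them: 20 per group, equal variances before and after, and the same before/after correlation rho at both times, varied from 0.5 to 0.9. The sample size has no effect size, SD or power behind it, so there is no figure of the plan to reproduce.

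**Variance of the acute-versus-late contrast.** With outcome variance 1 and n per group:
- difference of change scores: 2 × 2(1 − rho)/n
- ANCOVA of the post-TAVI value on group and baseline: 2(1 − rho²)/n
- ratio: (1 − rho²)/[2(1 − rho)] = (1 + rho)/2

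**Variance of each group's change.**
- own baseline only: 2(1 − rho)/20
- common baseline mean estimated from all 40: (1 − rho²)/20 + (1 − rho)²/40
- ratio: (1 + rho)/2 + (1 − rho)/4 = (3 + rho)/4, which a simulation confirmed (0.877, 0.924, 0.950 and 0.976 for the four rows below)

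| rho | contrast: (1 + rho)/2 | reduction | each change: (3 + rho)/4 | reduction |
|---|---|---|---|---|
| 0.5 | 0.750 | 25% | 0.875 | 12.5% |
| 0.7 | 0.850 | 15% | 0.925 | 7.5% |
| 0.8 | 0.900 | 10% | 0.950 | 5% |
| 0.9 | 0.950 | 5% | 0.975 | 2.5% |

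These formulas treat the regression on baseline as known. Estimating it from 40 patients gives back part of the gain, which matters most at rho 0.9.

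**What the contrast can detect.** For 80% power with 20 per group, the normal approximation is (1.960 + 0.842) × √(2/20) = 0.89 SD of the change; the exact t calculation gives 0.91. A within-group paired test needs (1.960 + 0.842)/√20 = 0.63 SD, or 0.66 by exact t.

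**If two separate results were read as a contrast.** When the true changes are equal and each paired test has power p, exactly one is significant with probability 2p(1 − p). A simulation with 20 per group gave:

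| true change (SD of change) | power of each test | exactly one significant | direct comparison significant |
|---|---|---|---|
| 0 | 5% | 9% | 5% |
| 0.30 | 25% | 37% | 5% |
| 0.45 | 48% | 50% | 5% |
| 0.626 | 76% | 37% | 5% |
| 0.80 | 92% | 14% | 5% |

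The 50% is the maximum of 2p(1 − p), reached at p = 0.5, and not a typical value. Without an effect size in the documents, the range of 9% to 50% is what can be stated.

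**The case against.** The strongest reply is that the plan answers the objectives it sets. The Introduction and section 2.2 speak of measuring acute and long-term changes, and the Discussion compares post-TAVI with pre-TAVI results. No hypothesis of acute versus late is stated, and the split exists to limit radiation. Much of this stands. A reader might infer that the investigators will compare p-values between the groups; no section says so, and the discordance figures bear only on that misuse. A reader might also call the baselines wasted. They are not: every patient has baseline indices and baseline CZT-SPECT, which can serve the correlation and ROC aim, and the gain from pooling them is modest.

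A second reply is that a group term or a longitudinal model may be in a statistical analysis plan that is not shown. That is possible. Section 2.9 does, however, state its test of change affirmatively, so the point concerns a stated choice and not mere silence.

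A third is that the missing-data sentence supports little. Labelling does not say that patients without a 6-month study are excluded. In a joint model such a patient contributes only a baseline value, so the late mean still rests on those who return.

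Finally, reading the test as within-group combines section 2.9 with the Limitations, because section 2.9 itself names neither grouping nor pairing. Mann–Whitney U is a test for independent samples, and its use on before/after values in the same patients is a separate and arguably clearer fault in that sentence.

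**Conclusion.** The point holds in a limited form. Randomisation to the time of reassessment is stated, the stated analysis of change makes no use of it, and no estimate of the difference between acute and late change is planned. The plan does not announce an invalid inference; it leaves any claim about that difference without support.

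The benefit of the better analysis is real but moderate, from the top of the table (rho 0.5) to the bottom (rho 0.9), and rests on the assumptions listed above. In standard errors, the best case is 1 − √0.75 = 13% for the contrast and 1 − √0.875 = 6% for each change. Even so analysed, the contrast in a study of 40 is for estimation and not for confirmation. Its value lies mainly in giving an honest interval where otherwise there would be none.

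**What to change.** In section 2.9, replace the before/after sentence with one model per index fitted to all randomised patients: a constrained longitudinal model with a common baseline mean and separate acute and 6-month means. ANCOVA of the post-TAVI value on group and baseline is an adequate simple version for the contrast. Report the acute change, the late change and their difference, each with a 95% CI. Label the difference exploratory, and state that nothing will be concluded from one change being significant and the other not. Say that the model assumes missing 6-month values are missing at random, and report how many patients in each group lack a follow-up value. Move the statement of randomisation into section 2.1, with the allocation ratio.

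If the investigators do not want the contrast, the minimum is a sentence saying that the two changes will be described separately and not compared.

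The cost is wording and a little analysis: no added patients, procedures or radiation.
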